# Protocol for a randomised trial testing a community fibrosis assessment service for patients with suspected non-alcoholic fatty liver disease: LOCal assessment and triage evaluation of non-alcoholic fatty liver disease (LOCATE-NAFLD)

**DOI:** 10.1186/s12913-020-05233-2

**Published:** 2020-04-21

**Keywords:** Non-alcoholic fatty liver disease, NAFLD, Community-based management, Protocol, Randomised controlled trials, Economic evaluation, Implementation evaluation

## Abstract

**Background:**

Non-alcoholic fatty liver disease (NAFLD) is the most common type of chronic liver disease in Australia and its recent increase mirrors the obesity and type 2 diabetes epidemics. Currently, many patients who present to primary care with abnormal liver function tests or steatosis on liver ultrasound are referred for assessment in secondary care. Due to the large number of patients with NAFLD, this results in long waits for clinical and fibrosis assessment, placing unnecessary burden on the public hospital system.

**Methods:**

We will conduct a 1:1 parallel randomised trial to compare two alternative models of care for NAFLD. Participants will be randomised to usual care or the LOCal Assessment and Triage Evaluation (LOCATE) model of care and followed for 1 year. We will recruit patients from the non-neighbouring Sunshine Coast and Metro South Hospital and Health Services (HHSs) in Queensland, Australia. Our primary outcome of interest is time to diagnosis of high-risk NAFLD, based on the number of participants in each arm of the study who receive a diagnosis of clinically significant fibrosis. Two hundred and 34 participants will give us a 95% power to detect a 50% reduction in the primary outcome of time to diagnosis of high-risk disease. We will also conduct an economic evaluation, evaluating the cost-effectiveness of the new model of care. We will also evaluate the implementation of the new model of care.

**Discussion:**

It is anticipated that the results of this study will provide valuable new information regarding the management of NAFLD in the Australian setting. A relatively simple change to care could result in earlier identification of patients with significant liver disease and lower overall costs for the health system. Results will be directly disseminated to key staff for further distribution to consumers, policy- and decision-makers in the form of evidence briefs, plain language summaries and policy recommendations.

**Trial registration:**

The trial was registered on 30 January, 2020 and can be found via ANZCTR - number ACTRN12620000158965.

## Background

Non-alcoholic fatty liver disease (NAFLD) is the most common type of chronic liver disease in Australia and its recent increase mirrors the obesity and type 2 diabetes epidemics [1, 2]. The prevalence of disease in Australia is approximately 30% of adults, comparable to other developed countries [3]. Currently, many patients who present to primary care with abnormal liver function tests or steatosis on liver ultrasound are referred for assessment in secondary care. Due to the large number of patients with NAFLD, this results in long waits for clinical and fibrosis assessment, placing unnecessary burden on the public hospital system. Depending on the presence of risk factors such as diabetes, 60 to 90% of patients with NAFLD do not have advanced fibrosis, are not at risk of chronic liver disease complications, and can be safely managed in primary care. At the other end of the risk scale, recent community-based studies have suggested that as many as 12 to 17% of primary care patients with NAFLD and type 2 diabetes may have clinically significant liver disease [4, 5]. The most important predictor of liver-related mortality is the extent of fibrosis – once NAFLD is identified, assessment of risk stratification is crucial to make decisions about management and referral. Due to the lack of risk stratification at primary care level, coupled with poor general practitioner knowledge about NAFLD [6], many patients with advanced disease may not undergo timely referral into secondary care. This exposes them to the risk of disease progression, decompensation and avoidable hospital admissions [7].

The predicted increases in NAFLD in the next decade will create demand on health services and have potentially large economic costs. As the number of NAFLD cases increase, the health system will incur increased costs associated with its diagnosis, management, and disease progression [8]. The estimated annual cost of liver diseases in Australia is $51 billion, of which NAFLD accounts for a considerable share [9], although few studies have reported economic outcomes [10].

NAFLD reduces health-related quality of life, particularly for those with severe disease who have higher complication risks. We propose that a community fibrosis assessment service will provide NAFLD patients with an integrated model of care, providing accurate stratification of disease risk, timely identification of advanced disease, and guidance for general practitioners (GPs) to enable better community management of mild disease. Gathering evidence from a prospective trial will address critical knowledge gaps in the Australian evidence-base and enhance the likelihood that the new findings will be implemented into routine practice.

### Hypothesis

The new model of care for NAFLD patients with fibrosis risk stratification of patients in the community will improve patient outcomes and be cost-effective, by more appropriately triaging NAFLD patients, reducing time to appropriate care, and avoiding unnecessary hospital appointments.

## Methods

### Study design

#### Parallel randomised trial

We will conduct a 1:1 parallel randomised trial to compare two alternative models of care for NAFLD. Participants will be randomised to usual care or the LOCal Assessment and Triage Evaluation (LOCATE) model of care and followed for 1 year to monitor their outcomes.

#### Reasoning

A parallel randomised trial is an excellent study design for estimating the benefits of a new model of care compared with a usual model of care. Randomising groups in parallel means that variables that change over time cannot confound the comparison of interest, because any changes are equally experienced by both groups.

#### Limitations

Randomised trials sometimes do not reflect real world settings because of their inclusion and exclusion criteria [11]. We aim to use as similar a patient group in the trial as would be eligible for the service in real life.

### Study setting

We will recruit patients from the Sunshine Coast and Metro South Hospital and Health Services (HHSs). These are non-neighbouring HHSs located in the south-east of Queensland. Combined, these HHSs provide healthcare to approximately 30% of Queensland’s population (1.4 M residents).

#### Potential for risk, burdens and benefits to participants

There is little risk for participants as the study involves either current usual care or a modification to a model of care that uses an established modality and treatment pathway. The study makes extensive use of routinely collected data, which reduces the burden on participants. Participants in the LOCATE model of care group may benefit from a faster diagnosis, as per our key study hypothesis.

#### Discontinuation of whole study

The study will only be discontinued if a regulatory body, funding body, or Human Research Ethics Committee (HREC) judges it necessary for medical, safety, regulatory, or other reasons consistent with applicable laws, regulations and good clinical practice.

### Study population

#### Patient inclusion criteria

Patients will be included if they:
Have had NAFLD diagnosed or suspected by their GP.Are aged 18 years or over.Understand the consent procedures and give their full consent.Consent to access of their data from Queensland Health and Medicare Benefits Schedule (MBS) and Pharmaceutical Benefits Scheme (PBS).

#### Patient exclusion criteria

Patients will be excluded if they:
Are pregnant.Have advanced cardiac disease or another terminal illness.Have high current alcohol consumption, defined as two or more standard drinks per day.Have Hepatitis B or C.Require priority review at the Hepatology Clinic, for instance, if liver imaging suggests cirrhosis or a focal liver lesion.Have been evaluated in a specialist hepatology clinic in the previous 12 months.Have plans to leave the area within the next 12 months.

The exclusion criteria are designed to reduce loss to follow-up and exclude patients who would be ineligible for a wider roll out of the service, or who require priority care and review.

### Aims

#### Primary clinical outcome

The time to diagnosis of high-risk NAFLD will be calculated based on the number of participants in each arm who receive a diagnosis of clinically significant fibrosis (transient elastography (TE) over 8.0 kPa) [7], with the time measured from date of GP referral to a confirmed diagnosis.

#### Secondary clinical outcomes

Secondary clinical outcomes of interest are:
Time to first successful fibrosis assessment with FibroscanReduction in hospital admissionsReduction in emergency department presentationsReduced time to additional screening/testing for liver diseaseImproved health-related quality of lifeReduced hepatocellular carcinoma (HCC) detected outside specific surveillanceReduced variceal bleeding occurring without variceal surveillanceIncreased statin useIncreased referrals to a specialist, other than a hepatologist, for example, to a dietician or exercise physiologistReduced mortality

#### Primary economic outcome

To evaluate the cost-effectiveness of the new model of care, where the costs and health outcomes associated with the LOCATE model of care are compared to those experienced under usual care.

#### Secondary economic outcome

We will model the potential for longer term cost-savings due to improved identification and stratification of high-risk NAFLD patients in the community and the reduction in high cost, hospital-based complications.

#### Implementation outcomes

To evaluate the implementation of the new model of care we will:
Map the reach of the model of care.Determine the impact of the model of care on the proportion of low risk and higher risk NAFLD being seen in specialist clinics.Determine if patients with low risk and high risk NAFLD received appropriate care for their condition.Determine the factors associated with implementation of the model of care including: (a) individual factors, (b) institutional factors and (c) systemic factors.Explore the GP and patient experience with the LOCATE model of care including acceptability of community-based screening and care for lower risk conditions.Determine whether LOCATE is a sustainable and scalable model of care in the community.

### Description of intervention and comparator

Participant progress through the study is shown in Fig. 1. The starting event is a patient visiting their GP where if there are enough concerns about the patient’s liver health, the GP will write a referral requesting a specialist hepatology clinic review/appointment. Referral letters will be screened by a hepatologist at the Sunshine Coast University Hospital and Logan Hospital hepatology clinics to identify potentially eligible patients.

**Fig. 1 Fig1:**
[figure not shown]
Recruitment and patient flow pathway for LOCATE-NAFLD study

#### Randomised to LOCATE

Study participants randomised to the new model of care will be invited to attend a local clinic to have their suspected NAFLD assessed with mobile transient elastography, using the Fibroscan machine. The invitation and assessment will be made by a specialist study nurse, who will write a report for the hepatologist. The hepatologist will triage patients to low- or high-risk, depending on the assessment of liver scarring and potentially other clinical indicators.

##### Low risk

Participants with a low Fibroscan score - TE under 8.0 kiloPascal (kPa) - will be classified as ‘Low Risk’. A letter will be sent to participants with a summary of their results and instructions on scheduling a GP appointment for review. A letter will be sent to the referring GP informing them of the results and with advice on multidisciplinary NAFLD management and guidelines for follow up [6].

These patients will remain on the waitlist to see a hepatologist at the hospital clinic as originally intended.

##### High risk

Participants with clinically significant fibrosis - TE over 8.0 kPa - will be classified as ‘High Risk’. Participants will be sent a letter summarising their test results and asking them to call the hospital hepatology clinic to arrange an appointment. GPs will be sent a letter informing them of the results and proposed management.

#### Randomised to usual care (comparator)

For those participants randomised to usual care, their referral letters will be dealt with in the usual way, and the patients will wait to see a hepatologist at the hospital clinic as originally intended.

#### Fibroscan service

The Fibroscan service will enable participants to undergo reliable assessment of the severity of liver fibrosis and to identify those with advanced fibrosis and cirrhosis who need both secondary care input and surveillance for liver cancer. The mobile Fibroscan clinics will occur on a rotational basis in the two regions using GP clinics and primary care facilities.

The Fibroscan will give the following test results:
Liver stiffness measurement - a marker of clinically significant fibrosis or advanced cirrhosis.Controlled attenuation parameter, to detect and quantify steatosis [12].

Examinations will be performed by a trained clinical nurse with extensive Fibroscan experience. Using an experienced operator is very important for producing reliable scans. Participants who did not attend an arranged appointment will be offered another appointment.

Around 7% of Fibroscans performed do not provide a valid reading. This is multifactorial, including issues such as skin to capsule depth, body habitus and rib spacing. These participants will be scheduled for a hepatology clinic visit as per the usual model of care. We will record the number of times the scan was unsuccessful and the reason why.

#### Other diagnostic information

Some additional information may be collected from GP referral letters if it is available. This information, including blood tests, may be used to help in triage and diagnosis, and may include:
Fibrosis-4 score.NAFLD fibrosis score [7].Enhanced Liver Fibrosis

### Description of all processes

#### Data collection

#### Referral letter

Date of referral, age, BMI, presence of type 2 diabetes and relevant blood tests such as AST, ALT, albumin, platelet count, viral serology, ferritin and transferrin saturation will be extracted from the referral letter.

#### Study questionnaire

The study recruitment questionnaire will contain:
Year of birth for calculating age.Gender.Height and weight for calculating BMI.Alcohol consumption in the past year using the 10-item screening tool, Alcohol Use Disorders Identification Test (AUDIT) [13].Current employment status for the economic analysis.EQ-5D-3 L [14] for estimation of health-related quality of life for the economic analysis.

#### Twelve-month telephone follow-up

Participants will be telephoned by study staff at 12 months post recruitment and asked:
EQ-5D-3 L questions for quality of life.Current employment status.

#### Twelve-month chart audit

Study nurses will audit the patients’ individual medical record at 12 months post-recruitment and extract much of the data needed for the primary and secondary outcomes.

#### Data management

#### Data sources

Data for outcomes involving contact with tertiary care will be collected from Queensland Health administrative databases.

For the economic evaluation, a state-based model will be developed. Costing data will be prospectively collected from multiple sources to measure costs associated with; hospital utilisation, pharmaceutical and primary care use, and patient travel costs, lost productivity and other out-of-pocket expenses. To estimate health utility, quality of life data will be collected using the EuroQol EQ-5D-3 L tool and assigned to each health state in the model. Data will be collected from participants at two time points, as previously described.

For the implementation objectives, we will audit data collected throughout the study, and conduct semi-structured interviews with key stakeholders and consumers. These interviews will occur within 8 weeks of the trial’s conclusion.

#### Participant data

Following recruitment and the return of the consent forms and baseline questionnaires to the study team, a research assistant will enter the data directly into the secure REDCap platform and determine whether participants meet the eligibility requirements according to the inclusion/exclusion criteria. The 12-month telephone survey will be entered directly into REDCap by the study staff.

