#### Recruitment and consent

#### Recruitment

Potential participants will be identified based on the referral letter sent from their GP to the hepatology clinic. Potentially eligible participants will be sent a letter containing an invitation to participate and the contact details of a study nurse.

NEGATIVE OR NO RESPONSE: If no response to the initial letter is received after 2 weeks, a study nurse will contact the patient by phone. If the potential participant does not answer the phone, an SMS will be sent from a study phone to their mobile, informing them that it was a study nurse who called, and providing a brief explanation of the study and contact information. If at any stage of this process they state they are not interested, they will not be contacted again.

POSITIVE RESPONSE: Those interested in participating will be able to call a study nurse to discuss the trial. Interested participants will then be mailed the Participant Information and Consent Form, MBS/PBS consent forms, withdrawal form, study questionnaires, a $20 voucher and a reply-paid return envelope.

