#### Randomisation

A 1:1 randomisation list will be created by the study statistician in the *R* software. The list will be stratified by health service (Sunshine Coast and Metro South) and will be in randomised blocks of size 6 and 8. This creates balanced groups over time and means that group sizes will be approximately equal if recruitment ends early. The list will be uploaded into the REDCap software [15]. Patients will be randomised once they have returned the signed consent form and questionnaires.

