#### Blinding

It is challenging to hide the randomised group because this is an open-label study where both the participants and researchers will be aware of what group participants are in. Baseline data will be collected blind to randomised group, as it will be done prior to randomisation.

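### The 12-month EQ-5D-3L is asked and recorded by study staff with no stated masking in an open-label trial, so interviewer knowledge of the arm can bias the quality-of-life comparison

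*Protocol article*

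**What the plan says.** **Baseline.** The recruitment questionnaire contains the "EQ-5D-3 L [14] for estimation of health-related quality of life for the economic analysis" (Protocol article, Study questionnaire). It is sent by post: "Interested participants will then be mailed the Participant Information and Consent Form, MBS/PBS consent forms, withdrawal form, study questionnaires" (Recruitment). Allocation follows its return: "Patients will be randomised once they have returned the signed consent form and questionnaires" (Randomisation). The Blinding section draws the consequence: "Baseline data will be collected blind to randomised group, as it will be done prior to randomisation".

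**Twelve months.** "Participants will be telephoned by study staff at 12 months post recruitment and asked" the EQ-5D-3L questions and current employment status (Twelve-month telephone follow-up). On recording, "The 12-month telephone survey will be entered directly into REDCap by the study staff" (Participant data).

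**Who knows the allocation.** The Blinding section describes an open-label study in which "both the participants and researchers will be aware of what group participants are in". It claims no masking for any measurement after baseline. Of the randomisation list, the article says "The list will be uploaded into the REDCap software" (Randomisation), so allocation and the 12-month survey sit in the same system.

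**Use of the data.** Analyses of secondary outcomes specifies a linear regression of the 12-month quality-of-life result, adjusted for baseline. Data sources assigns EQ-5D-3L utilities to the health states of an economic model and lists lost productivity among the costs.

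**The concern.** Quality of life is a listed secondary outcome, and its only post-randomisation value is spoken to, and typed in by, a member of the study team. Someone who knows the participant's group can prompt, clarify or code answers differently by arm without intending to. The Blinding section treats open-label delivery as the reason masking is difficult. That reason applies to participants, who cannot be masked to where and when they are scanned. It does not apply to the person making a telephone call a year after recruitment. Interviewer awareness is a separate source of bias and can be reduced separately.

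At stake is the between-arm quality-of-life estimate. A systematic shift moves the estimate and its confidence interval together, and a larger sample would not correct it. Employment status comes from the same call and was collected at baseline for the economic analysis, so it is exposed to the same interviewer.

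**Working it through.** The plan gives no figure to reproduce here. The check is a reading of the sections against each other, followed by an illustration of size.

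**Reading the sections together**

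1. Baseline EQ-5D-3L is self-completed on a mailed form before allocation exists, so no interviewer effect can enter it.
2. The 12-month EQ-5D-3L is interviewer-administered, and the only statement about awareness after randomisation is that researchers know the group.
3. The analysis compares 12-month scores between arms given baseline. A shift common to both arms, such as one due to moving from post to telephone, cancels. A shift that depends on the interviewer knowing the arm does not cancel. Baseline carries no information about it, so adjustment leaves it in the treatment coefficient.
4. In the economic model, utilities attach to health states. If a state's utility is shared by the arms, a distorted answer in one arm moves the value used for both. The effect on incremental results then depends on how each arm is spread over the states, and its sign cannot be read from the documents.

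**Illustration of size**

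From the article: target 234 (117 per arm), minimum 156, two-sided 5% level, 5% censored by death or loss to follow-up (Sample size and statistical power; all given for the primary outcome). Assumed, because the documents give none: EQ-5D SD 0.20, baseline-to-12-month correlation 0.6, differential bias 0.02, no true effect.

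- SE of the adjusted difference = SD × √(1 − ρ²) × √(2/n) = 0.20 × √(1 − 0.36) × √(2/117) = 0.20 × 0.8 × 0.1307 = 0.0209.
- Standardised bias = 0.02/0.0209 = 0.956.
- P(|Z + 0.956| > 1.96) = Φ(−1.004) + Φ(−2.916) = 0.159, against 0.05 with no bias.
- With a bias of 0.03 the same formula gives 0.300.

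The protocol aims not to present p-values in external papers. The same probability is the chance that the reported 95% interval excludes zero when there is no true difference.

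**Sensitivity.** Work in SD units, with 5% loss, so n = 0.95 × N/2 per arm and SE = √((1 − ρ²) × 2/n). A bias of 0.02 with SD 0.20 is 0.1 SD.

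| N | ρ | bias 0.05 SD | bias 0.1 SD | bias 0.2 SD |
|---|---|---|---|---|
| 234 | 0.5 | 7.1% | 13.8% | 40.6% |
| 234 | 0.7 | 8.2% | 18.1% | 55.1% |
| 156 | 0.5 | 6.4% | 10.8% | 29.0% |
| 156 | 0.7 | 7.1% | 13.6% | 39.9% |

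Allowing for loss changes little. The result is driven by the assumed bias.

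**The case against.** **The size is assumed throughout.** SD, correlation and bias are all outside the documents. This stands: the percentages show what a given bias would do, not how large it is in this trial.

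**Operational detail belongs elsewhere.** The Data access section leaves access processes to a data management plan, and caller rotas and scripts are the kind of detail an article omits. Holding the list in REDCap does not show that a caller sees the allocation. This narrows the point but does not remove it, because the Blinding section says positively that researchers know the group and limits blind collection to baseline.

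**Participants are unmasked anyway.** True, and their own reporting bias would remain. That is no reason to leave a second, avoidable source in place.

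**Scope.** Quality of life is one of ten secondary clinical outcomes, and the primary clinical outcome is not affected. This stands.

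Three stronger readings are tempting, and the documents do not support them:

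- A reader might infer that the callers are the nurses who scanned LOCATE participants, so that only one arm talks to a familiar person. The article says only that study staff call. It also mentions a research assistant, and study nurses may telephone patients of both future arms during recruitment. In-person study contact is described for LOCATE alone, but who calls at 12 months is not stated.
- A reader might infer that the change from post to telephone is itself a bias. It applies to both arms, so alone it does not distort the comparison. Posting the 12-month form would also be a trade-off: telephoning non-responders would mix modes, and return rates could differ by arm.
- A reader might infer a QALY gain or a lower cost per QALY for LOCATE. That presumes an arm-level calculation, whereas the article describes utilities by health state.

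**Conclusion.** The point holds as a limited, avoidable weakness in outcome assessment. The only post-randomisation EQ-5D-3L, together with employment status, is obtained by study staff in a trial whose researchers know the allocation, and no masking of that interviewer is stated. The between-arm quality-of-life regression can be biased by this, and baseline adjustment does not protect it. Any effect on the economic evaluation is indirect and of unknown direction.

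The size cannot be derived from the documents. Under the assumed SD of 0.20, correlation of 0.6 and 117 per arm, a differential bias of 0.02 would take the false-positive rate from 5% to about 16%. With 5% loss and correlations of 0.5 to 0.7, the same bias gives about 14% to 18% at 234 participants and 11% to 14% at 156. The case for a change rests on the low cost of the remedy, not on these percentages.

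**What to change.** Amend Twelve-month telephone follow-up, Participant data and Blinding to say that:

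- the telephone call is kept for all participants in both arms;
- it is made by existing staff who neither invited nor scanned the participant, for example the research assistant who enters the baseline data;
- the caller reads a fixed script;
- the caller uses a REDCap role that hides the allocation and the scan forms, with the setting carried into the data management plan;
- the caller records whether the participant's group became known during the call.

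The cost is a rota constraint and a permission setting, using existing staff. Some participants will reveal their group, which the last item makes visible. Reporting bias from participants knowing their own group remains and should be acknowledged as a limitation.
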